## Abstract

**Background:**

In the era of High-sensitive troponin (hs-Tn), up to 50% of patients with a mild increase of hs-Tn will finally have a normal invasive coronary angiogram. Fractional Flow Reserve (FFR) derived from coronary computed tomographic angiography (FFR-CT) has never been used as a non-invasive tool for the diagnosis of coronary artery disease in patients with high-risk acute coronary syndrome without ST segment elevation (NSTE-ACS).

**Aims:**

The study aims to determine the role of coronary CT angiography and FFR-CT in the setting of high-risk NSTE-ACS.

**Methodology:**

We will conduct a prospective trial, enrolling 250 patients admitted with high-risk NSTE-ACS who will rapidly undergo a coronary CT angiography and then a coronary angiography with FFR measurements. Results of coronary CT, FFR-CT and coronary angiography (± FFR) will be compared.

**Potential significance:**

In conclusion, non-invasive identification of patients with high-risk NSTE-ACS who could avoid coronary angiography would reduce procedure related risks and medical costs.

## Introduction

1

Patients admitted to the emergency department (ED) for chest pain are a top priority, the early diagnosis of a myocardial infarction (MI) being key for the prognosis of the patient. Unlike myocardial infarction with ST segment elevation (STEMI) where the diagnosis is usually straightforward after electrocardiogram (ECG) analysis, acute coronary syndrome without ST segment elevation (NSTE-ACS) patients represent a major diagnostic challenge. Indeed, clinical assessment and ECG alone are not sufficient to confirm or exclude diagnosis in most patients. Therefore, the addition of blood test such as troponin remains the cornerstone of an early diagnosis and subsequent adequate treatment especially regarding the decision to send the patient to the catheterization laboratory for a coronary angiography. The recent introduction of high-sensitive troponins (hs-Tn) has considerably improved diagnostic sensitivity of NSTE-AC. However, this comes at a cost as a high proportion of these patients will finally have a ‘normal’ invasive angiography (up to 50% among patients with an increase of troponins of ≤3x the upper range limit (URL) according to the recent fourth universal definition of myocardial infarction from the European guidelines [1]).

As troponin alone seems to be insufficient to correctly identify patients in real need of a coronary angiography, alternative diagnostic strategies are critically needed in order to avoid multiple unnecessary exams. In that sense, the identification on a non-invasive tool able to identify patients in whom coronary angiography will not allow to reveal a significant stenosis would be time, resources and cost saving.

Fractional Flow Reserve (FFR) derived from coronary computed tomography (CT) is a technique developed to calculate non-invasively the hemodynamic impact of a stenosis based in coronary geometries extracted from conventional CT images. The value derived from the blood flow simulation can be interpreted in the same way as the invasive FFR, which is the gold standard of coronary hemodynamics assessment. To date, no study has evaluated the benefit of FFR-CT in NSTE-ACS patients.

We designed this trial to assess whether FFR-CT is able to identify among high-risk NSTE-ACS patients, those without hemodynamically significant coronary stenosis by invasive FFR.

## Methods

2

### Study population

2.1

Detailed inclusion/exclusion criteria are reported in Table 1. Patients intended to be enrolled in the study must be ≥18 years old and have to present a rise and/or fall of high-sensitive cardiac troponins T (hs-cTnT, Roche, Switzerland) values measured on at least 2 timepoints with at least one value above the 99th percentile of the URL. They must also present with symptoms of ischemia and/or new or presumed new significant ST-segment–T wave changes on ECGs.

**Table 1 t0005:** Complete list of inclusion/exclusion criteria.

**Inclusion criteria:**
≥18 years old patients
Presenting a rise and/or fall of high-sensitive cardiac troponins T (hs-cTnT) values measured on at least 2 timepoints with at least one value above the 99th percentile of the URL and with at least one of the following:
Symptoms of ischemia
New or presumed new significant ST-segment–T wave (ST–T) changes
Informed consent signed
Presumed availability for follow-up up to 1 year

**Exclusion criteria:**
STEMI patients
Estimated glomerular filtration rate (eGFR) of <45 ml/min
Presence of very high-risk criteria:
Hemodynamic instability or cardiogenic shock
Recurrent or ongoing chest pain refractory to medical treatment
Life-threatening arrhythmias or cardiac arrest
Mechanical complications of MI
Acute heart failure
Recurrent dynamic ST-T wave changes, particularly with intermittent ST-elevation
Pregnant and breast-feeding women (women of child bearing potential must have a negative urine or blood pregnancy at screening)
Contra-indication to beta-blocker and/or nitroglycerin
Patients with diagnosis made using a troponin dosage other than hs-cTnT
Patients with prior coronary artery bypass grafting (CABG)
Patient with known severe heart failure (i.e Ejection fraction of left ventricle of <30%)
Patient incapable of judgement or under tutelage
Patient in emotional distress or other unstable psychical condition incompatible with informed consent signature

STEMI patient will not be included as well as, severe renal failure, pregnant and breast-feeding women, patients with diagnosis made using a troponin dosage other than hs-cTnT, patients with prior coronary artery bypass grafting (CABG), and patient with known severe heart failure. Importantly, patients presenting one or more very high-risk criteria according to the 2018 European guidelines on myocardial revascularization [2], and the 2014 American guidelines on NSTE-ACS [3] and thus requiring coronary angiography within 2 h will also be excluded. These criteria are the presence of hemodynamic instability or cardiogenic shock, recurrent or ongoing chest pain refractory to medical treatment, life-threatening arrhythmias or cardiac arrest, mechanical complications of MI, acute heart failure, and recurrent dynamic ST-T wave changes, particularly with intermittent ST-elevation

### Study design and procedure

2.2

The present study is a single arm, double blinded, prospective trial. A summary of study procedure and schedule is provided in Table 2**.**

**Table 2 t0010:** Detailed study procedure.

	Screening		D0	D1	D3	1 month	6 months	12 months
**General evaluation**		**Inclusion**						
Informed consent (study-related)	x^1^							
Demographic data / Medical history (SoC)	x							
Eligibility criteria (study-related)	x^1^							
**Laboratory tests**								
Creatinine (SoC)	x		x		x			
Pregnancy test (study-related)	x							
**Clinical evaluations**								
History / Symptoms assessment (SoC)	x					x	x	x
Physical examination (SoC)	x		x			x	x	x
Electrocardiogram (SoC)	x		x	x	x	x	x	x
Bicycle test (SoC)								x
Echocardiogram (SoC)							x	
**Diagnosis procedures and measures**								
Coronary-CT (study-related)			x^2^					
Coronary angiography, Invasive FFR (SoC)			x^2^					
FFR-CT and FFRangio (study-related)			Between D0 and D14					
**Safety**								
AEs of interest: acute kidney failure, vascular complications, stroke (study-related)			x	x	x			
AEs of interest: MACEs (study-related)			x	x	x	x	x	x
SEs (study-related)			x	x	x	x		

1 Patients will be first pre-selected based on patient's file, and patients meeting main eligibility criteria will be informed about the study. After patient signed the informed consent, all eligibility criteria will be formally checked, and patients meeting all eligibility criteria will be included. ^2^Coronary CT should be done before coronary angiography, and both should be done within 24 h from patient initial admission to ED. SoC: standard of care, AEs: adverse events, SEs: serious events.

Patients admitted to hospital with high-risk NSTE-ACS and who accept to participate to the study will undergo a coronary CT angiography within 23 h after diagnosis in order to have time to proceed to coronary angiography within the recommended window time of 24 h. After realization of the CT, they will benefit from guidelines recommended treatment including a coronary angiography. According to internal and international guidelines, all efforts will be made to perform the coronary angiography within 24 h of ACS diagnosis [2], [3].

The coronary CT angiography procedure takes approximately 1–2 h (including logistical organization and patient transportation), and all efforts will be made not to delay the coronary angiography compared to patients who would not participate in the study. At the time of coronary angiography, patients will be blinded from the CT results as well as the direct treating physician and interventional cardiologist realizing the procedure, in order to avoid any influence in patients’ management. The procedure will be done using a 256-slice multi-detector CT (GE Healthcare Revolution CT, Chicago, Illinois, USA). Just before the examination, as routinely done for this non-invasive test to allow for optimal coronary vasodilation and visualization, oral Metoprolol (25–50 mg) will be administered if necessary to ensure a heart rate of 65 bpm or lower as well as one unique dose of sublingual nitroglycerine (400–800 mg) [4], [5], [6]. Parameters used for CT acquisition will be as following [7]: 100 kVp/550 mA for BMI < 25 (high definition mode), 100 kVp/550 mA for BMI included between 25 and 30, 120 kVp/600 mA for BMI > 30 (standard definition mode). Off line, an FFR-CT will be calculated with the data of the coronary CT angiography by blinded investigators in a central FFR-CT core laboratory (HeartFlow ®, Redwood City, CA 94063, USA). In parallel an FFRangio™ analysis will also be conducted on the invasive coronary angiography images [8]. Hemodynamically significant lesion will be defined as lesion with an FFR-CT value of ≤0.80.

During the invasive coronary angiography, FFR will be measured in all lesions with a visual diameter stenosis ≥30% using the PressureWire™ X Guidewire (Abbott, Chicago, Illinois, USA) with the following protocol: first, equalization of the pressure wire and the aortic pressure will be performed at the tip of the guide catheter prior to all measurements. Second, the pressure wire will then be advanced distal to the stenosis. Third, hyperemia will be obtained using intracoronary adenosine (150mcg for the right coronary artery and 200mcg for the left descending or the circumflex coronary arteries). Fourth, at the end of the procedure, the absence of a drift will be confirmed after a pull-back of the pressure to the same location as the initial equalization. Hemodynamically significant lesion will be defined as lesion with an FFR value of ≤0.80.

Of note, in case of coronary angiography showing no obstructive coronary disease, and thus not offering satisfactory explanation for the myocardial injury, patients will undergo cardiac magnetic resonance imaging (CMRI), to detect a potential alternative diagnosis (myocarditis, Takotsubo…). This later examination will however be left to treating physician’s discretion depending on the clinical context.

Both angiography-derived FFR (FFRangio™) and FFR derived from FFR-CT will be measured in the same position as invasive FFR and compared with this latter as gold standard.

### Hypothesis and study endpoints

2.3

The hypothesis to be tested is that FFR-CT might have an interest in three aspects of the management of high-risk NSTE-ACS patients:(1)FFR-CT discriminates those without any significant lesions defined by a negative invasive FFR value (>0.80) among all lesions with ≥30% diameter stenosis by invasive angiographic evaluation.(2)FFR-CT discriminates those with a significant lesion (defined by a positive invasive FFR (≤0.80).(3)When a clear culprit-lesion is evident (i.e. sub-occlusive vessel and ECG changes in the same territory), FFR-CT helps for the management of the non-culprit lesions (good correlation compared to invasive FFR).

Co-primary endpoints will be negative predictive value of coronary CT angiography and FFR-CT as compared to angiography with FFR and accuracy, sensitivity, specificity and positive predictive value of FFR-CT as compared to angiography with FFR.

Secondary endpoints will be (1) correlation of FFR-CT as compared to invasive FFR in lesions with at least a 30% stenosis, (2) negative predictive value of coronary CT as compared to angiography, (3) accuracy, sensibility, specificity and positive predictive value of coronary CT as compared to angiography, (4) accuracy, sensibility, specificity, negative predictive value and positive predictive value of FFRangio™ as compared to angiography (5) a priori treatment decision after angiography versus treatment decision according to invasive FFR, (6) a priori treatment decision after angiography versus treatment decision according to FFRangio™, (7) a priori treatment decision after angiography versus treatment decision according to FFR-CT, (8) natural history of deferred lesions according to invasive FFR, FFR-CT, CT and FFRangio™ in term of MACE

The following safety endpoints will be systematically recorded: Radiation dose received per patient (mSv), contrast media dose received per patient (ml), incidence of acute kidney failure defined as an increase of >1.5x the baseline creatinine value 3 days after the coronary-CT, incidence of vascular complications related to the coronary angiogram, incidence of stroke and incidence of major cardiac adverse events (MACE, composite outcome including cardiovascular death, myocardial infraction, and urgent revascularization).

### Follow-up

2.4

Follow-up will be organized 1 month (±7 days), 6 months (±14 days) and 12 months (±14 days) after the acute coronary syndrome. These visits will include a detailed history, as well as physical examination and ECG. During the second visit, a transthoracic echocardiography will be performed, and a treadmill exercise stress test will be performed during the third visit. Study flow chart is presented in Fig. 1.

**Fig. 1 f0005:**
[figure not shown]
Flow-chart for patients included in the study.

### Data and statistical analysis

2.5

Statistical analysis will be carried out using SPSS 25.0 software (SPSS Inc., Chicago, Illinois) and Stata 14.3. Comparisons of characteristics of patients will be performed using Chi-squared tests for qualitative variables and Student’s t or Mann-Whitney tests as appropriate. Confidence intervals (CI) for proportions (sensitivity, specificity, accuracy) will be calculated using the Wilson Score method. With the last iteration of the FFR-CT software, the per-patient sensitivity and specificity were 86% (95% CI: 77% to 92%) and 79% (95% CI: 72% to 84%) [9]. In the recent VERDICT trial based on NSTEMI patients [10], 12% had 3 vessel disease, 23% 2 vessel disease (which included left main), 34%, 1 vessel disease, 30% nothing, Thus, out of 100 patients with 300 coronaries, we expect 106 (i.e. 36 + 46 + 34) vessels with a stenosis. Based on the FAMOUS NSTEMI trial [11], 60% of invasive FFR measurements of these stenoses were significant [12]. Thus, with a standard error of 0.05, and for a power of 80%, 204 patients will be required. However, some of the CT will not be suitable for analysis and some patients will have to be excluded. Therefore, we plan to include 250 patients. Of note, these number is also in line with the literature investigating the accuracy of FFR-CT versus FFR in patients with stable coronary artery disease [9], [13]. For the treatment decision based on the various methods, McNemar's test will be used.

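### Hypothesis 3 on non-culprit lesions is judged by correlation pooled over all lesions, which cannot show agreement; if vessel or lesion proportions are reported, their Wilson intervals also need a clustering adjustment

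*Protocol article*

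**What the plan says.** Protocol article, Hypothesis and study endpoints (2.3). The third hypothesis applies where a culprit lesion is clear and states that "FFR-CT helps for the management of the non-culprit lesions (good correlation compared to invasive FFR"). The first secondary endpoint is "correlation of FFR-CT as compared to invasive FFR in lesions with at least a 30% stenosis". It is not limited to non-culprit lesions, and none of the other listed endpoints is either. The co-primary endpoints are predictive values, sensitivity, specificity and accuracy against angiography with FFR.

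Study design and procedure (2.2). Invasive FFR is measured in every lesion of at least 30% diameter stenosis, FFR-CT is read at the same position, and 0.80 is the cut for both. One patient can therefore contribute several lesions.

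Data and statistical analysis (2.5). "Confidence intervals (CI) for proportions (sensitivity, specificity, accuracy) will be calculated using the Wilson Score method". The sentence names no unit. The next sentence gives planning values of 86% and 79%, labelled per patient. The text then counts vessels: "12% had 3 vessel disease, 23% 2 vessel disease (which included left main), 34%, 1 vessel disease, 30% nothing", and "60% of invasive FFR measurements of these stenoses were significant". It ends with patients: "with a standard error of 0.05, and for a power of 80%, 204 patients will be required".

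**The concern.** Hypothesis 3 is about management: whether FFR-CT can stand in for invasive FFR when deciding on a non-culprit lesion. That decision turns on which side of 0.80 the value falls, so the two methods must agree in absolute value near the cut. The article's criterion has two defects.

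- **Wrong kind of measure.** Standard correlation coefficients are unchanged by a constant shift. FFR-CT could be biased, misclassify many lesions and still correlate well. Bias is a realistic possibility here. Clinical relevance (3.3) reports only moderate FFR-CT accuracy in non-culprit lesions after STEMI, suggests altered vessel volume as a reason, and says it is unknown whether the same holds in NSTE-ACS.
- **Wrong set of lesions.** The endpoint mixes in culprit lesions. Study limitations (3.2) expects many severe culprit stenoses. These stretch the FFR range and can raise r without any better performance in the lesions that hypothesis 3 concerns.

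Hypothesis 3 could thus be declared supported on evidence that does not bear on it.

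A smaller, conditional concern is that the Wilson interval assumes independent observations. Lesions and vessels from one patient need not be independent.

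**Working it through.** **1. What a constant shift does to r and to classification.** Adding a constant b to FFR-CT changes neither its variance nor its covariance with invasive FFR, so r is the same for any b.

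Inputs: 60% of stenoses at or below 0.80 (section 2.5). The SD of FFR is not given, so 0.10–0.15 is assumed, with a normal distribution and no error other than the shift. The mean is 0.80 − 0.2533 × SD. If FFR-CT reads 0.05 low, lesions with true FFR between 0.80 and 0.85 become falsely positive. Their share is Φ(0.2533 + 0.05/SD) − 0.60:

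| SD | share misclassified |
|---|---|
| 0.10 | 0.774 − 0.600 = 0.174 |
| 0.12 | 0.749 − 0.600 = 0.149 |
| 0.15 | 0.721 − 0.600 = 0.121 |

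A shift of the same size in the other direction turns lesions between 0.75 and 0.80 falsely negative. Their share is 0.60 − Φ(0.2533 − 0.05/SD), which gives 0.197, 0.165 and 0.132.

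**2. The same with measurement noise.** This is a simulation with assumed FFR mean 0.80, SD 0.12 and noise SD 0.06:

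| FFR-CT bias | r | concordance coefficient | sensitivity at 0.80 |
|---|---|---|---|
| 0 | 0.887 | 0.88 | 0.85 |
| +0.05 | 0.887 | 0.81 | 0.67 |
| +0.10 | 0.887 | 0.66 | 0.45 |

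**3. What a wider FFR range does to r.** With noise SD 0.06, r = SD/√(SD² + 0.06²). An FFR SD of 0.10 gives 0.10/0.1166 = 0.86, and an SD of 0.15 gives 0.15/0.1616 = 0.93. The measurement error is identical in both.

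The share of culprits in the pool can be illustrated from section 2.5. Per 100 patients, 12 × 3 + 23 × 2 + 34 × 1 = 116 stenosed vessels lie in 12 + 23 + 34 = 69 patients. (The article prints the total as 106, although its own terms add to 116.) If each of the 69 had one culprit vessel, 69/116 = 59% of the pooled vessels would be culprits and 47 would be non-culprit.

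**4. Clustering, only if vessel or lesion proportions are reported.** The size-weighted number of stenosed vessels per diseased patient is (12 × 9 + 23 × 4 + 34 × 1)/116 = 234/116 = 2.017. It depends only on the 34/23/12 mix, so the 106/116 discrepancy does not affect it.

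- Accuracy uses all stenosed vessels: excess cluster size 1.017.
- Sensitivity uses FFR-positive vessels (60%): 0.6 × 1.017 = 0.610.
- Specificity uses FFR-negative vessels (40%): 0.4 × 1.017 = 0.407.

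The last two assume that FFR positivity is spread independently over a patient's vessels. The design effect is 1 + excess × ICC, and the interval widens by about its square root. The documents give no intra-patient correlation, so 0.1–0.5 is assumed:

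| measure | design effect, ICC 0.1 to 0.5 | interval wider by |
|---|---|---|
| sensitivity | 1.061 to 1.305 | 3% to 14% |
| specificity | 1.041 to 1.203 | 2% to 10% |
| accuracy | 1.102 to 1.509 | 5% to 23% |

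For scale, 204 patients at the printed 1.06 vessels per patient give 216 vessels, of which about 130 are FFR-positive. A sensitivity of 0.86 then has a Wilson interval of 0.790–0.909. At ICC 0.5 it becomes 0.778–0.915.

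The 204 itself cannot be reproduced from the stated inputs, since no alpha, null value or tested parameter is given. Nothing above depends on how it was derived.

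**The case against.** **Classification at 0.80 is already assessed.** The co-primary endpoints are accuracy measures, with 0.80 as the cut for both methods, so a marked shift would show there. Secondary endpoints on treatment decisions, with McNemar's test, add to this. This stands for the overall lesion set, and it would be wrong to infer that the plan never examines misclassification. It does not rescue hypothesis 3, because none of these results is stated for non-culprit lesions. The decision endpoints also compare each method with the decision after angiography, not FFR-CT with invasive FFR directly.

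**The coefficient and the handling of several lesions belong in the analysis plan.** This is fair. A reader might infer a plain Pearson correlation that treats lesions as independent, but the article names no coefficient or model. If the unseen plan defines correlation as a concordance coefficient, bias would be penalised and the first defect would soften. The pooling would remain. What the article does fix is the criterion itself, and the usual coefficients (Pearson, Spearman) share the blindness to a shift.

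**Wilson intervals are right for patients.** This also stands. A reader might infer that vessel and lesion results use Wilson intervals and that coverage therefore falls well below 95%. The document does not say so. The Wilson sentence has no unit, the adjacent planning values are per patient, and hypotheses 1 and 2 sort patients. One might also call the trial sized on vessels, but the calculation mixes per-patient accuracy, vessel counts and a number of patients. Larger losses of coverage would need all three vessels of every patient to be analysed. FFR is measured only in lesions of at least 30%, and no convention for unmeasured vessels is stated.

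**Conclusion.** The point on hypothesis 3 holds whatever the unit of analysis. Its stated criterion cannot detect systematic bias, and its only matching endpoint is not confined to the lesions it concerns. An unseen 0.05 low bias would misclassify about 12–17% of lesions. This rests on the article's 60% positive share and on an assumed normal FFR distribution with SD 0.10–0.15. The effect of culprit lesions on r is shown in direction only, because the article gives no FFR spread by lesion type.

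The interval point is conditional and modest. Per patient there is no problem. At vessel or lesion level the intervals would be too narrow if intra-patient correlation is positive, by the amounts in the table, and those rest on an assumed correlation of 0.1–0.5. The documents do not support a statement that the plan's intervals are invalid as they stand.

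**What to change.** - Restate the criterion for hypothesis 3 and secondary endpoint 1 as mean bias (FFR-CT minus invasive FFR) with Bland-Altman limits of agreement, using a patient random effect to allow for several lesions per patient.
- Add classification agreement at 0.80.
- Report both separately for non-culprit lesions, as the test of hypothesis 3. Correlation can stay as a descriptive figure.
- State the unit for the Wilson intervals and keep them for per-patient measures. For any vessel- or lesion-level sensitivity, specificity or accuracy, use GEE with robust variance or a bootstrap that resamples patients.

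Cost: analysis wording only. No new measurement or extra patient is needed. Intervals at vessel or lesion level become slightly wider, and the non-culprit results rest on fewer lesions than the pooled ones.

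### The sample-size argument in section 2.5 mixes per-patient accuracy with vessel counts, while the aim and hypotheses 1 and 2 classify patients

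*Protocol article*

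**What the plan says.** The protocol article points to the patient as the unit in two places. The Introduction gives the aim as to "identify among high-risk NSTE-ACS patients, those without hemodynamically significant coronary stenosis by invasive FFR". In section 2.3, hypothesis 1 reads "FFR-CT discriminates those without any significant lesions defined by a negative invasive FFR value (>0.80) among all lesions with ≥30% diameter stenosis", and hypothesis 2 is its counterpart for those who have a significant lesion. Hypothesis 3 is about lesions: "FFR-CT helps for the management of the non-culprit lesions (good correlation compared to invasive FFR".

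The endpoint sentence in section 2.3 begins "Co-primary endpoints will be negative predictive value of coronary CT angiography and FFR-CT as compared to angiography with FFR" and goes on to the accuracy, sensitivity, specificity and positive predictive value of FFR-CT. It names no unit.

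Section 2.5 builds the sample size in four steps:

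- It quotes the accuracy of the latest FFR-CT software: "the per-patient sensitivity and specificity were 86% (95% CI: 77% to 92%) and 79% (95% CI: 72% to 84" (percent).
- It takes 12%, 23% and 34% of patients with three-, two- and one-vessel disease and turns these into vessels: "Thus, out of 100 patients with 300 coronaries, we expect 106 (i.e. 36 + 46 + 34) vessels with a stenosis".
- It takes 60% of the invasive FFR measurements of those stenoses to be significant.
- With a standard error of 0.05 and 80% power, it arrives at 204 patients, raised to 250 for unusable scans and exclusions.

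**The concern.** Sensitivity and specificity measured on patients describe how patients are classified. They do not go with a disease frequency counted in vessels or in FFR measurements. Section 2.5 puts all three into one argument and gives the answer in patients, so the reader cannot tell which quantity the 204 is meant to estimate, or in what unit.

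This matters most for the NPV, the first co-primary measure listed and the figure that would support sparing a patient angiography. NPV rises as prevalence falls. A vessel denominator brings in many undiseased vessels, some from patients who have a significant lesion elsewhere. It therefore gives a higher NPV with a narrower interval than the patient-level figure that the decision needs. The article itself warns, under Study limitations, that a false-negative FFR-CT may do more harm here than in stable angina. If the planning unit stays ambiguous, the more flattering figure could be taken as the answer to hypothesis 1.

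**Working it through.** **Inputs, all from section 2.5.** Sensitivity (Se) 0.86 and specificity (Sp) 0.79, per patient. One-, two- and three-vessel disease 34%, 23% and 12%. Share of stenoses with FFR ≤0.80: 60%. Patients: 204, hence 612 vessels at three each.

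**The plan's own figures.**
- The printed terms 36 + 46 + 34 sum to 116, not 106.
- The 204 does not follow from the stated rule, because no null or target value is given for the 80% power. On the printed 106 there are 1.06 × 0.6 = 0.636 positive vessels per patient. A standard error of 0.05 on Se needs 0.86 × 0.14/0.05² = 48 positives, or about 76 patients. A 95% half-width of 0.05 needs 185 positives, or about 291 patients.
- A 90% half-width of 0.05 needs 130 positives, or 130.3/0.636 = 204.9 patients. That comes close, but it uses no power, is not the stated rule, and may be chance among many variants tried.

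Both are separate errors and carry no weight below.

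**Formula.** NPV = (1 − p)Sp / [(1 − p)Sp + p(1 − Se)], where p is the prevalence in the chosen unit.

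**Per vessel, counting vessels without a wire as negative.**
- With 106 stenosed vessels: p = 0.6 × 106/300 = 0.212. NPV = 0.788 × 0.79 / (0.788 × 0.79 + 0.212 × 0.14) = 0.6225/0.6522 = 0.954.
- With 116: p = 0.232 and NPV = 0.949.
- Using 106, about 612 × 0.6522 = 399 vessels test negative. The Wilson 95% CI, ignoring clustering, is 0.93 to 0.97.

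**Per patient (positive if any stenosis is positive).**
- Stenoses independent: p = 0.34 × 0.6 + 0.23 × (1 − 0.4²) + 0.12 × (1 − 0.4³) = 0.5095. NPV = 0.3875/(0.3875 + 0.0713) = 0.845.
- Full within-patient correlation: p = 0.69 × 0.6 = 0.414. NPV = 0.4629/(0.4629 + 0.0580) = 0.889.
- Highest p when every stenosis has a 60% chance of being positive: p = 0.34 × 0.6 + 0.23 + 0.12 = 0.554. NPV = 0.3523/(0.3523 + 0.0776) = 0.820.

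**Per-patient precision with 204 analysable patients.**

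| Case | FFR-positive / FFR-negative patients | Test-negative patients | NPV (Wilson 95% CI) |
|---|---|---|---|
| Full correlation | 84 / 120 | 106 | 0.889 (0.815–0.935) |
| Independent | 104 / 100 | 94 | 0.845 (0.758–0.904) |
| Highest p | 113 / 91 | 88 | 0.820 (0.726–0.886) |

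Under independence the standard errors are √(0.86 × 0.14/103.9) = 0.034 for sensitivity, √(0.79 × 0.21/100.1) = 0.041 for specificity and √(0.8445 × 0.1555/93.6) = 0.038 for NPV. All are below the 0.05 that section 2.5 names.

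**The case against.** The strongest reply is that the unit is clear enough. The aim, hypotheses 1 and 2, the quoted accuracy and the final sample size are all in patients. A condensed article may leave the choice between per-patient and per-vessel analysis to the full protocol or analysis plan, and neither is shown. This stands in part: the silence of the endpoint sentence would not be a finding by itself. It does not rescue section 2.5, where inputs in different units are combined on the page.

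A reader might go further and infer that the co-primary predictive values are counted in three units: patients, vessels and wire positions. The documents do not support that. Section 2.2 says that FFR-CT and FFRangio values "will be measured in the same position as invasive FFR and compared with this latter as gold standard". This is a rule for matching measurements. It also covers FFRangio, which is in no co-primary endpoint, and it fits hypothesis 3 and the secondary correlation endpoint. The vessel count is a planning input and does not define an endpoint.

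The figures are also open to challenge. The documents give no per-vessel accuracy, so the vessel NPV applies per-patient values where they do not strictly belong. Wires go only into lesions of at least 30% diameter stenosis, so counting every other vessel as negative is an assumption. A patient prevalence of 69%, with every diseased patient positive, should not be used as the upper end. It requires every single-vessel stenosis to be positive, and it is impossible on the printed vessel count, which yields only 63.6 positive vessels per 100 patients.

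Finally, if about 130 positives were the planning target, the patient unit would need about 130/0.51 = 255 analysable patients. The article states no such target, so a need for more patients cannot be inferred.

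**Conclusion.** The point holds as a mismatch in section 2.5. Per-patient accuracy is joined to a vessel count and a per-measurement positivity rate, in support of a trial whose aim and first two hypotheses classify patients, and the endpoint sentence does not settle the unit.

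The illustrated size is an NPV of about 0.95 per vessel against about 0.845 per patient. In other words, roughly 5% of negative vessels but 15% of negative patients would be false negatives. Even the most favourable per-patient case, 0.889, stays below the vessel figure. The comparison rests on equal sensitivity and specificity in both units, on vessels without a wire being negative, and on a 60% chance of positivity for every stenosis. It is not a forecast of the trial's results. The 106 versus 116 slip barely affects it (0.954 against 0.949).

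**What to change.** In section 2.3, state that all co-primary measures are per patient: reference-positive if any lesion has invasive FFR ≤0.80, otherwise reference-negative. Make per-vessel and per-lesion results secondary, with intervals that allow for clustering within patients.

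In section 2.5, replace the vessel-based denominator with the expected numbers of FFR-positive and FFR-negative patients: about 104 and 100 of 204 under independence, with the range shown. Then restate the precision that 204 analysable patients give, for example a per-patient NPV of 0.845 with a Wilson 95% CI of about 0.76 to 0.90.

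The cost is wording in two sections and one restated precision figure, with no added patients or procedures. The downside is that the stated NPV and its interval look less favourable than a vessel-level figure. The vessel sum and the derivation of 204 need their own corrections.
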